### Intervention description

Needs Rounds are monthly hour-long triage meetings focused on 8–10 residents in each care home who are at risk of dying without a plan in place. A checklist^25^ is used to identify the most appropriate residents to discuss. Needs Rounds are chaired by a palliative care specialist and attended by care home staff who discuss each resident’s physiological, psychosocial and spiritual needs. This instigates a number of tailored actions, which are always personalised for the individual, including medication reviews, case conferences, anticipatory/advance care planning and referrals to relevant specialists.

Needs Rounds have a strong evidence base to support their uptake. Research in Australia demonstrated a number of positive outcomes. Needs Rounds reduced the length and number of hospitalisations,^26 27^ increased resident dying in their preferred place,^26^ with dignity, compassion and comfort,^28^ enabled staff to normalise death and dying,^29^ and improved workforce confidence.^28^

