### Outcomes

The primary outcome is to determine *what works, for whom, in what circumstances,* for UK Needs Rounds. Secondary outcomes focus on health service use, alongside quality of death and dying, staff capability to adopt a palliative approach, and family perceptions of care. The core economic outcome is the total change in health and social care service costs that result from the intervention.

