Family perceptions of care will be captured from relatives of residents who are discussed at Needs Rounds, using the CANHELP lite.^42^ Twenty-two items from the second half of the questionniare will be used to collect family self-reported data of satisfaction with care. The Cronbach’s alpha for the total score is 0.88–0.94. A family will only be asked once to complete this measure, even if the resident is discussed at Needs Rounds more than once.

Resident data collection will focus on demographic information and health service use (table 2). Data will be collected from the care homes by care home staff. Training will be provided to ensure robust data collection and reporting. This will be summary level data to ensure anonymity.

**Table 2 T2:** Resident data collection

Type	Variables
Demographic information	Age Ethnicity First language Charlson Comorbidity Index
Deaths	Number of deaths Preferred place of death Actual place of death
Health service use	Clinical role seen in primary care Hospital admissions: Name of hospital Duration of admission Specialty/ward Mode of transport to hospital
Assessments and interventions triggered by Needs Rounds	Physical assessments Clinical investigations, for example, blood/urine tests Referrals to other NHS services Changes in medicines Syringe drivers

Economic evaluation will be based on the intervention and health service cost elements identified in tables 3 and 4. The costs of hospitalisation will be constructed from resident-level data on length of stay collected by the care homes, and costed using the National Tariffs and hospital specific Patient Level Information and Costing System data for both England and Scotland. Total costs for the each of the pre and post periods will be calculated by summing these costs across all residents admitted to hospital from a given site; the benefit is the difference between prehealth and posthealth service-use costs.

**Table 3 T3:** Intervention cost elements

Cost type	Cost detail	Measurement of costs
Direct costs	Intervention costs on-site: Staff time Travel Consumables and equipment Workshop costs	Included within the project budget and therefore directly recorded. Where appropriate additional detail will be collected directly from the care homes.
	Additional NHS staff time attending care home Additional prescriptions	Estimated in the SoECAT, with additional costs recorded by intervention staff as required.

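### The only medicines item in the cost tables counts added prescriptions, with no matching credit for medicines stopped or reduced, although the economic outcome is a total change in cost

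*Protocol article*

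**What the plan says.** Four parts of the protocol article bear on this.

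- **Intervention description.** The tailored actions that follow a Needs Rounds meeting are listed as "including medication reviews, case conferences, anticipatory/advance care planning and referrals to relevant specialists".
- **Outcomes.** The core economic outcome is the "total change in health and social care service costs that result from the intervention".
- **Data collection.** The scope of the costing is set in one sentence: "Economic evaluation will be based on the intervention and health service cost elements identified in tables 3 and 4". In Table 3 the relevant row reads "Additional NHS staff time attending care home Additional prescriptions", so its medicines item is "Additional prescriptions", and its measurement column reads "Estimated in the SoECAT, with additional costs recorded by intervention staff as required". Table 4 covers ambulance journeys, hospital stays, primary care usage and care home costs connected with admissions. It has no medicines line. Table 2 includes "Referrals to other NHS services Changes in medicines Syringe drivers" under the heading for assessments and interventions that Needs Rounds set off.
- **Estimating the cost effectiveness.** Benefit is defined broadly as the change in NHS costs. It is then estimated from fewer hospital stays and days, valued with day rates and ambulance costs. Taxi transfers and primary care use are added where the data allow.

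**The concern.** A medication review can add, stop or alter items. The listed cost element looks only at additions, and its measurement column also speaks only of additional costs. A total change needs both directions. If the tables are followed literally, the medicines line can register an increase in spending but never a decrease.

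The line would feed the net benefit, which the article projects over 5 years to all care home beds in England and in Scotland. The range to be reported around that projection comes from the 95% CI of the treatment effect on hospital use. It would not reveal an asymmetry in how a cost item was defined. The direction of each medicine change also has to be captured when the data are collected. Resident data are held at summary level, so direction may not be recoverable later.

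**Working it through.** The article gives no figure for medicines (no number started or stopped, no unit cost, no duration), so there is nothing to reproduce. The check sets the passages side by side and follows a stopped medicine through each possible route into the calculation.

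**Routes for a stopped or reduced medicine**

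| Possible route | What the article lists | Does it carry the saving? |
|---|---|---|
| Table 3 prescriptions row | Additions only, with additional costs recorded | Not as worded |
| Table 4 | Ambulance, hospital stay, primary care usage, care home costs linked to admissions | No medicines line |
| Primary care usage | The related Table 2 variable is the clinical role seen, which describes contacts rather than items prescribed; the proforma itself is not itemised | Not stated |
| Pre and post cost totals | Summed over residents admitted to hospital | No route for a resident who was never admitted |
| Before-and-after comparison of medicines | Table 2 lists medicine changes only as triggered by Needs Rounds; no pre-implementation medicines data are listed | No |
| Open list of further costs | Taxis and primary care use given as examples | Medicines not named |

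No listed item carries the saving, and no sentence rules it out.

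**Direction on the medicines line.** Let A be the cost of medicines added and S the cost avoided through medicines stopped or reduced, both zero or more.

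- Change required by the stated outcome: A − S.
- Amount the row counts as worded: A.
- Difference: A − (A − S) = S ≥ 0.

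The row therefore overstates medicine cost by S, which counts against Needs Rounds. It is exact only if S = 0.

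**Direction for overall net cost.** Table 2 also records clinical investigations and referrals to other NHS services triggered by Needs Rounds. Neither has an explicit line in Table 3 or Table 4. Let U ≥ 0 be whatever part of their cost goes uncounted.

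- Overstatement of net cost from these items together: S − U.

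The article gives neither S nor U, so the sign of S − U is unknown.

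**The case against.** The strongest reply is that this infers an exclusion from silence. *Additional* can be read as incremental, meaning net of anything withdrawn. Benefit is defined as the change in NHS costs, the list of further costs is open-ended, the primary care proforma is not itemised, and the NICE Reference Case is to be followed wherever possible. Whether a cost row is scored net is the kind of detail a journal article may leave to a fuller economic plan. Any error on this line is also conservative: it understates the benefit and cannot create a false saving.

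Much of that stands as a limit on the claim. A reader might infer that savings on medicines are barred from the analysis, but no sentence says so. A reader might also take Table 2 to record every medicine change, but its heading restricts the item to changes triggered by Needs Rounds. And a reader might conclude that the whole net cost is tilted against the intervention. The uncosted investigations and referrals could pull the other way, so the document does not support that.

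What does not stand is the claim that the text already resolves the point. None of the generous readings is stated. The article does set out its cost elements and ties the evaluation to them, and the stated element does not match the stated outcome. That is a mismatch in what is written, not a request for omitted detail.

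**Conclusion.** The point holds as a minor costing correction. Read as written, the medicines line is one-directional, and on that line alone it overstates cost against Needs Rounds whenever a review stops or reduces a medicine. This rests on two readings: that the row means additions, as its wording and measurement column suggest, and that Tables 3 and 4 define the costing, as the article says.

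The size cannot be given. It would need the number of medicines started and stopped, their unit costs and the durations, and the article contains none of these. It also does not say how often reviews stop medicines. The effect could be trivial or material, and nothing here shows which. The direction of any bias in overall net cost is likewise not established.

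**What to change.** 1. In Table 3, reword the prescriptions row to *net change in prescriptions triggered by Needs Rounds*. Cost items started, stopped and changed with their sign.
2. In the Table 2 item on changes in medicines, record direction (started, stopped, changed) as summary-level counts, and state that these counts feed the Table 3 row. Summary counts are consistent with the article's position that resident data are anonymous and collected without individual consent.
3. State one assumption on unit cost and on how long a change is taken to last, and apply it alike to starts and stops.

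The cost is one reworded row, a direction field on an item already planned, and a little more recording by care home staff. The result will depend on the unit cost and duration assumption, because summary counts do not hold drug-level detail, so that assumption should be reported with the result. The change makes only the medicines line two-directional; it does not settle how triggered investigations and referrals are costed.

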### Analysis

Fidelity will be assessed through analysis of a random sample of 20% of all audio-recorded Needs Rounds to assess adherence to the agreed approach developed in the workshops. A three-tier scoring system will be adopted, of 1 (high adherence), 2 (moderate), 3 (low), with operational definitions for these scores developed prospectively as UK Needs Rounds are developed.

Transcripts of audio data and documentary evidence will be stored and organised using NVivo. Within and between case analysis will be conducted inductively, drawing on process tracing and constant comparative methods, respectively. Differences between the Australian context and the UK will be surfaced to facilitate detailed reporting on the specificity of the UK model to the local context. i-PARIHS will also be used to structure the analysis, and deductive analysis employed to refine the CMO theories. Thematic analysis will underpin the analytic approach, and follow the five-step process outlined by Braun and Clarke.^43^

CAPA, QODDI and CANHELP will be analysed with t-tests and presented using descriptive statistics, with statistical significance level set at p 0.05.

### Economic analysis: estimating the treatment effect of the intervention on health service outcomes

Data on the number and duration of hospitalisations for all care home residents will be captured for the 4 months prior to implementation, and in months 9–12 of delivery. This allows time for the intervention to be established and ensures that equivalent 4 month periods are compared with control for seasonality.

The treatment effect will be estimated as paired t-tests of the rate of hospitalisation, and number of hospital days, respectively. Multilevel regression modelling of the two outcome measures will be conducted, controlling for local area deprivation, sector of the care home, and other characteristics to describe the wider factors associated with the changes in the outcomes observed. A weighted least squares model of the outcomes will be estimated, with cases weighted by the number of beds in the care homes as a further robustness check. The estimates of the treatment effect will be used in the cost effectiveness analysis, incorporating the uncertainty of the estimates in the analysis.

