### Estimating the cost effectiveness of the intervention on health service outcomes

A cost–benefit analysis (CBA) of the intervention will be undertaken. The cost calculation will include both direct and indirect costs to both NHS and care homes delivering the intervention. Benefits are calculated as the change in NHS costs incurred following the intervention. This will be estimated by valuing the reduction in hospital stays and hospital days as a result of the intervention. These will be measured using hospital day rates and ambulance costs. Where possible, data will also be collected on additional costs, such as hospital transfers via taxi and primary care use.

The CBA will be conducted from the perspective of the NHS and Personal Social Services. The costs of the intervention will be compared with the changes in health service costs from reduced hospitalisation. The costs and benefits will be calculated taking account of (1) uncertainty in the estimate of the treatment effect; (2) projected costs over a 5-year period; and (3) spatial variation in cost across jurisdictions. Wherever possible the analytical specification will follow that of the National Institute of Health and Care Excellence (NICE) Reference Case.^44^ While there are also likely to be individual and broader societal benefits arising from the intervention, these are challenging to value in financial terms and beyond the scope of this economic evaluation. They will be explored through the qualitative data collection.

The net benefits of the intervention will be modelled over a 5-year period separately for care homes in (1) England and (2) Scotland, given the estimate of cost savings per care home bed and the total number of care home beds in each jurisdiction, and applying an annual discount rate. These predictions will be modelled at the point estimate for the treatment effect, and also for the upper and lower bounds of the 95% CI around the treatment effect, to provide a range of plausible costs savings over 5 years incorporating the uncertainty in the main study.

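### For the admission rate, the estimate that feeds the saving per bed counts every care home equally, and the bed-weighted estimate is kept only as a robustness check

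*Protocol article*

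**What the plan says.** The economic analysis section of the protocol article defines the effect: "The treatment effect will be estimated as paired t-tests of the rate of hospitalisation, and number of hospital days, respectively". No weighting is mentioned, so each home counts once. The same paragraph adds a multilevel model, to describe factors associated with change, and a weighted least squares model, "with cases weighted by the number of beds in the care homes as a further robustness check". It then links the effect to the economics: "The estimates of the treatment effect will be used in the cost effectiveness analysis, incorporating the uncertainty of the estimates in the analysis".

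The section on estimating cost effectiveness projects net benefit over five years, "given the estimate of cost savings per care home bed and the total number of care home beds in each jurisdiction". On which value is projected it says: "These predictions will be modelled at the point estimate for the treatment effect"; both 95% confidence limits are used as well. The benefit is the reduction in hospital stays and days, of which it says: "These will be measured using hospital day rates and ambulance costs".

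The data collection section gives a second route to the benefit. Costs before and after are obtained by "summing these costs across all residents admitted to hospital from a given site", and the difference is taken. The article does not say how either route becomes a saving per bed.

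**The concern.** The projection needs a quantity that can be multiplied by a number of beds: total change divided by total beds. The estimator named for the admission rate gives the change in the average home, in which a small home weighs as much as a large one. The two differ when the per-bed effect varies with home size.

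The article gives some reason to think it may. The intervention is the same for every home: "Needs Rounds are monthly hour-long triage meetings focused on 8–10 residents in each care home". The sample size paragraph expresses the worthwhile change as one admission per typical home in four months, and Table 1 asks for homes of varied size. If averted admissions are roughly constant per home, the per-bed effect is larger in small homes, and equal weighting gives those homes too much influence on a per-bed figure. The same mismatch would pass into both confidence limits, and so into the cost-effectiveness range and the five-year projection.

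**Working it through.** **Inputs from the article (Target sites and population).** 30 homes; mean 52 beds; 0.173 emergency admissions per bed in four months; target change 0.02 per bed; SD of change 0.040; α 0.05; power 80%. The spread of home sizes is not given, so CVs of 0.2 to 0.7 are assumed below.

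**The plan's own figures.**
- 0.173 × 52 = 9.0 admissions per home, and 0.02 × 52 = 1.04, about one admission per home. Both agree with the text.
- Paired normal formula, two-sided: n = ((1.960 + 0.842) × 0.040 / 0.02)² = 31.4, so 32, close to the stated 30. Power at 30 homes is 78.2%. The calculation therefore fits an unweighted analysis with the home as unit.

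**The two estimators.** Let home i have bᵢ beds and avert cᵢ admissions, so its rate change is dᵢ = cᵢ/bᵢ.
- Unweighted: U = mean(dᵢ).
- Per bed: W = Σcᵢ / Σbᵢ, the bed-weighted mean of dᵢ.
- Hence U − W = −cov(b, d) / mean(b), which is zero only when d and b are uncorrelated.

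**Same number averted in every home (cᵢ = 1).** U/W = mean(1/b) × mean(b), which is 1 + CV² for lognormal sizes. W = 1/52 = 0.0192.

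| Assumed CV of size | U | U/W |
|---|---|---|
| 0.2 | 0.0200 | 1.04 |
| 0.3 | 0.0210 | 1.09 |
| 0.5 | 0.0240 | 1.25 |
| 0.7 | 0.0287 | 1.49 |

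Simulated samples of 30 homes give 1.087 at CV 0.3 and 1.241 at CV 0.5. The shape of the size distribution also matters. With 15 homes of 26 beds and 15 of 78 (CV 0.5), U = (1/26 + 1/78)/2 = 0.0256, and U/W = 1.33.

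**Same per-bed effect in every home.** U = W, so there is no difference.

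**Per-bed effect proportional to size.** With dᵢ = 0.02 × bᵢ/52 and the 26/78 homes, U = 0.020, W = 0.02 × 3380/2704 = 0.025 and U/W = 0.80. Here U is 20% too low.

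**Hospital days.** These are named as a number, not a rate. If tested as counts per home, mean change divided by mean beds = (Σ/30)/(Σb/30) = Σ/Σb, which is already the per-bed figure. The difference is 0%.

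**Effect on the total saving.** If a share s of the saving is valued through admissions and the rest through days as counts, the total is overstated by s × (U/W − 1). The article gives no s. Taking s from 0.1 to 1 as an assumption, and equal gains per home, the overstatement runs from 0.9% to 9% at CV 0.3 and from 2.5% to 25% at CV 0.5.

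**The case against.** Four arguments stand wholly or in part.

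1. **Days drive hospital cost.** The costing is built on length of stay and a day rate. On the text as written, the admission rate seems to enter mainly through ambulance journeys. A reader might infer that the headline saving itself is overstated by the percentages in the table. The document does not support that: they apply to the admission rate, and reach the whole saving only if days are also analysed as a rate per bed.
2. **The route to a per-bed figure is inferred.** The article lists several models and a summed-cost route, and never spells out the conversion. Summed costs divided by beds would already be bed-weighted. The inference is nevertheless well supported, because the treatment effect and its confidence limits are named as what is projected.
3. **The direction is not settled.** The fixed monthly hour need not cap the benefit. Table 1 expects 1500 residents discussed, about 1500/30 = 50 per home against 52 beds, and twelve rounds of 8–10 give 96–120 places. Gains in staff knowledge could also reach the whole home. A constant per-bed effect is therefore possible.
4. **Bed weighting does not guarantee the national figure.** Recruitment favours larger homes. If each home averts one admission and the national mean size were 40 beds (an assumption), the national value would be 1/40 = 0.0250, and the sample's 0.0192 would be 23% too low. This limits what the fix achieves; it does not make the unweighted mean a per-bed quantity.

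It is also fair that a weighted model is already planned, so a divergence on rates would show. What remains unsettled is which estimate is carried forward.

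**Conclusion.** The point holds in a limited, conditional form. For the hospitalisation rate, the estimate named as the treatment effect is an average over homes, whereas the projection uses it per bed, and the estimator that matches the projection has only a secondary role.

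If each home averts a similar number of admissions, the unweighted figure exceeds the sample's per-bed change by about CV²: about 9% at CV 0.3 and 25% at CV 0.5. This rests on assumed, roughly lognormal home sizes. The excess is zero with a constant per-bed effect and changes sign if the effect rises with size. For days counted per home and divided by mean beds there is no mismatch, so the consequence for the total saving may be much smaller. The documents do not establish that the five-year projection is overstated, nor by how much.

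**What to change.** In the two economic analysis sections, state that the bed-weighted change (total before minus total after, divided by total beds) and its 95% CI feed the per-bed saving, the cost-effectiveness range and the five-year projection. Apply this to both admissions and hospital days, and define days per bed. Say how this agrees with the summed-cost route under data collection. Keep the unweighted paired t-test as the result for the average home and as the sensitivity analysis. Add that, because recruitment favours larger homes, the national projection still assumes a per-bed effect that does not depend on home size.

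The cost is wording only. The weighted model is already planned and, fitted to home rate changes without covariates, gives exactly total change over total beds. If counts are roughly Poisson and the per-bed effect is constant, it is also slightly more precise: the unweighted standard error is about √1.154 = 1.07 times as large at an assumed CV of 0.4. The small downside is that a few large homes carry more weight, which the unweighted result will reveal.
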